## Abstract

**Background:**

Associated with a tripling in obesity since 1970, type 2 diabetes mellitus (T2DM) in children has risen 9-10 fold. There is a critical need of protocols for trials to prevent T2DM in children.

**Methods/Design:**

This protocol includes the theory, development, evaluation components and lessons learned from a novel YMCA-based T2DM prevention intervention designed specifically for high-BMI African American children from disadvantaged, inner-city neighborhoods of Oakland, California. The intervention was developed on the basis of: review of epidemiological and intervention studies of pediatric T2DM; a conceptual theory (social cognitive); a comprehensive examination of health promotion curricula designed for children; consultation with research, clinical experts and practitioners and; input from community partners. The intervention, *Taking Action Together*, included culturally sensitive and age-appropriate programming on: healthy eating; increasing physical activity and, improving self esteem.

**Discussion:**

Evaluations completed to date suggest that *Taking Action Together *may be an effective intervention, and results warrant an expanded evaluation effort. This protocol could be used in other community settings to reduce the risk of children developing T2DM and related health consequences.

**Trial registration:**

ClinicalTrials.gov NCT01039116.

## Background

There is a critical need for trials to be conducted that aim to identify strategies to prevent T2DM mellitus (T2DM) in children. Associated with a tripling in obesity since 1970, T2DM in children has risen 9-10 fold [1]. Additionally, nearly 1 in 6 overweight youth has pre-diabetes [2]. African American youth are among the highest for risk of T2DM with higher rates of obesity and insulin-resistance than other ethnic groups due, in part, to being more insulin resistant [3]. Nearly 50% of African American children born in the U.S. in 2000 are expected to develop diabetes in their lifetimes [4].

*Taking Action Together *(*TAT*) was a controlled community-based intervention protocol developed by researchers at U.C. Berkeley in partnership with the YMCA of the East Bay to reduce risk of T2DM among low-income, high BMI, 9-10 year old African American children through improvements in nutrient intake, physical activity, and self esteem. To avoid stigmatization due to body fatness, focus was placed on improving diet and physical activity rather than on weight loss. Described are the rationale, theory, design, development, implementation, evaluation components, and lessons learned from *TAT*.

This protocol was designed for delivery to low-income African American children living in disadvantaged, inner-city neighborhoods such as those of East or West Oakland, CA. Compared to a White child living in the Oakland hills (comparatively higher income area), those African American children are more likely to be born low birth weight, live in a low-income household, have parents with only a high school education or less, and have poor access to healthy foods [5].

There is a dearth of culturally sensitive interventions that target obesity, diabetes, diet or physical activity among African American youth [6], especially for those living in disadvantaged neighborhoods. Out-of-school settings represent a widely accessible, but largely untapped and under-researched, venue for T2DM prevention. In the U.S. there are ~3,000 YMCA sites serving nearly 10 million children [7]. Out-of-school programs typically have more flexibility than schools and may be better able to include health-related activities. While healthy benefits from out-of-school programs have been reported [8-12], more studies in 'real world' settings are needed to translate research findings into practice to stem the rapid increase in T2DM.

### Hypotheses and specific aims

Consistent with social cognitive theory, we postulated that development of self efficacy with respect to targeted behaviors would improve children's dietary intake, physical activity, and self esteem which, in turn, would reduce insulin resistance in part by stabilizing body weight. Thus, our main hypothesis was that children in the treatment group would show more favorable changes in insulin resistance than children in the control group following 1 or more 2 years in the program. A secondary hypotheses was that there would be greater improvements in the treatment group in dietary intakes and physical activity. A third hypothesis stated that early markers of behavioral change (dietary and physical activity self efficacy, self esteem, positive behaviors and communications) would be improved in the treatment group when compared to the control.

Thus, the specific aims were (1). To assess the influence of treatment group status on change in insulin resistance (fasting HOMA-IR), (2). To determine the influence of treatment group status on change in intermediate outcomes (diet and physical activity), and (3). To determine the influence of treatment group status on change in potential moderating or mediating variables (self esteem, self efficacy, psychobehavioral characteristics).

## Methods/Design

### Selection Criteria (eligibility)

Inclusion criteria for child participants included: ancestry including at least one African American biological parent; being 9 to 10 years old; having BMI at or above the 85th percentile [13]; free of any systematic disorder or medication known to affect energy metabolism or body weight; and free of severe physical or emotional conditions that could interfere with study participation. The lower limit placed on age was based on concerns that the parents of younger children may be reluctant to consent to a blood draw, and on our assessment that the ethical risk-benefit ratio was less favorable in younger children. The upper limit was placed to avoid having to sub-group children according to age, loosing statistical power. Broader age ranges would need to be evaluated in subsequent studies.

### Primary outcomes

Change in insulin resistance over 1 or 2 yr of intervention was the primary outcome measure. Fasting glucose and insulin values were used to calculate the homeostatic model parameter - HOMA-IR, defined as fasting glucose (mmol/l) × insulin (μU/ml)/22.5 [14] and used as an index of insulin resistance [15]. Fasting indices of insulin resistance have been shown to be well correlated with estimates obtained using the "gold standard" methods of assessing insulin resistance using the euglycemic-hyperinsulinemic clamp in 9 - 10 year old children [16] and oral glucose tolerance test in premenarchal girls [17], and these indices have been used to show that overweight children are at greater risk for type 2 diabetes than normal weight children [18]. Lower risks are associated with this fasting index since it requires only a single veinpuncture and, thus, is preferable for use in children. The study's second primary outcome, change in glycosylated hemoglobin (HbA1c), was assessed by quantifying HbA1c using a dual HPLC method which detects variants common in African Americans that interfere will interpretation of HbA1c data [19,20].

### Demographic and Secondary outcomes

*Anthropometric variables *(Table 1), including child body weight and height, were measured and used to calculate BMI and BMI z-score. Additionally, waist and hip circumferences, and percent body fat were measured.

**Table 1 T1:** Evaluation Measures in *Taking Action Together*

Measurement	Procedure &/or reference
**Anthropometry (child)**	
Waist & hip circum and ratio	With plastic non-elastic tape [50]
Weight, height, BMI and BMIz	Wt: digital electronic scale, Ht: portable stadiometes, BMIz Calc [13]
% Body fat	BIA [50], % Body Fat Horlick's equation [51,52]
**Glucoregulation (Child)**	
Fasting Glucose, Insulin	Commercially available kits [50]
HOMA-IR	Calculation of insulin resistance [14]
HbA1c, C-Peptide, NEFA	HbA1c [19,20]; C-Pep & NEFA, (Linco & Wako kits).
Acanthosis nigricans	Appearance of skin on back of neck with 0-4 scale of severity [53]
**Diet (child)**	
Dietary intakes	Food diary [54,55]; average intake and servings [36]
Dietary habits & Nutrition knowledge	After-School Student Questionnaire self-efficacy [50,56]
**Physical Activity and Fitness (child)**	
Physical activity & fitness	3-day PA diaries [55], Lap run [57]
PA habits & knowledge	California Dept. of Education's Healthy Kids Survey [58]
Athletic competence	Harter self-perception profile for children [59]
**Self efficacy**	
Diet self-efficacy	ASSQ self-efficacy questions [56]
PA self-efficacy	Child's Self-Assessment for Physical Activity (CSAAPA) [57,60]
**Self-esteem & Body Image (child)**	
Self-worth & social acceptance	Harter self-perception profile for children [59]
Body satisfaction	Validated in African American adults [61], modified [62]
Self-esteem	Behavioral Assessment System for Children, BASC-2 [34], child report
**Behavior and Communications (child)**	
Conduct problems & activities	BASC-2 [34], parent report and child report
Communication & social skills	BASC-2 [34]; parent and child report
**Adult and Family Assessments**	
Family food behaviors	Shopping, meal preparation and family eating [63]
Change for diet and PA	Fruit & vegetables [64], avoidance of high-fat [64,65], exercise [66]
Family PA habits & weight	Family member's habits, duration of activity, and prevalence of overweight [50]
**Additional Potential Confounding Variables**	
Family environment & SEI	Moos Family Environment Scale [67], Socioeconomic index [63]
Family & Intrauterine history of T2DM	American Diabetes Association instrument [68]
Polyovarian syndrome	(female child participants only) [50]
Pubertal stage	Estradiol (E2), luteinizing hormone [50,69]

*Hematological variables *other than the primary outcomes previously described, included measurement of non-esterified fatty acid (NEFA) concentrations, which were used to calculate adipocyte fatty acid insulin sensitivity (ISI-FFA) by the formula:[2/(insulin × NEFA) +1] [21]. Additionally, pubertal stage was estimated following assessment of fasting plasma concentrations of specific sex hormones (Table 1).

*Dietary variables *included calculation of nutrient intakes and servings of foods consumed by children, following data analysis from 3-day food diary records (Table 1). Additionally, assessments were made of child food habits, preferences, self efficacy and nutrition knowledge; and of family food habits and stages of change with respect to specific healthy food habits.

*Physical activity *of child participants was assessed from 3-day physical activity diary records, and physical fitness was assessed using the Pacer lap run test that is administered as part of the California Fitnessgram evaluations (Table 1). Additionally, child physical activity habits, knowledge, competence and self efficacy were assessed using subjective questionnaires.

*Psychosocial variables *were assessed using subjective questionnaires administered to the child and/or parent (Table 1). These variables included measures of self esteem, body satisfaction, behavior and communications.

*Sociodemographic factors *were measured using subjective questionnaires administered to an adult family member. Factors of interest included age and gender of adults, education, housing and employment status.

*Other subjective data *were obtained also from questionnaires administered to the adult family member. Factors of interest included family history and intrauterine risk of T2DM, diagnoses of girls for polyovarian syndrome, and selected characteristics of the family environment.

### Theoretical model

Recognizing the interplay between individual characteristics and one's social environment in determining health-related behaviors, Bandura's Social Cognitive Theory (SCT) was selected as the foundation for *TAT *[22]. In youth, modest improvements in social, cognitive, dietary and exercise outcomes have been achieved when programs utilized SCT [23,24]. Consistent with SCT, we postulated that strong self efficacy would positively affect diet quality, physical activity and energy balance of children which, in turn, would reduce insulin resistance directly or indirectly via effects on body fatness (Figure 1). An extensive research literature has demonstrated that several factors (e.g., child pubertal stage, self esteem, psycho-behavioral status) are able to interfere with or promote these relationships.

**Figure 1 F1:**
[figure not shown]
**Theoretical model for *Taking Action Together *study**.

### Intervention goals

The development of the *TAT *intervention was informed by a comprehensive review of the literature in conjunction with recommendations from a panel of national experts on policy and program initiatives to prevent T2DM in children [25]. The review revealed that the most efficacious programs aimed to improve both diet and physical activity.

#### Dietary goals

Based on a 2003 review of the dietary determinants of obesity [26], the following dietary goals were selected for *TAT*: increase intake of fruit, vegetables, whole grains, and low-fat dairy foods; reduce intake of high-fat and high-sugar foods and beverages; and sharpen awareness of cues to satiety.

#### Physical activity goals

It has been recommended that children participate in a cumulative total of 60 minutes or more daily of moderate-to-vigorous physical activity [27]. To promote sustained adoption of an active lifestyle, activities should be both fun and doable by children; and overweight children should begin physical activities at a low intensity and duration, gradually increasing as competence is gained [28]. The *TAT *physical activity goal was to increase time spent in moderate-to-vigorous intensity physical activity by developing skills, knowledge and self efficacy with respect to having endurance and being flexible, strong, coordinated, quick and agile.

#### Self-esteem goals

Studies have shown that overweight children tend to have lower body satisfaction and, in some cases, lower self esteem than normal weight children [29]. Exposure to teasing exacerbates the effect [30]. Poor self esteem is often associated with negative behavior [29]. Further, emphasis was placed on self-esteem building since poor self esteem can interfere with the development and maintenance of positive eating and physical activity behaviors, and since efforts to improve these behaviors can unintentionally negatively influence self esteem. Our goal for the self-esteem component was to develop five social and emotional competencies:awareness of one's strengths, challenges, behaviors and styles of interacting; ability to effectively interact and communicate with others; respect for self and others; ability to describe self using art, writing and verbal means; and ability to assess positive change in one's behavior and personal interactions. Consistent with the tenet of 'health at every size' [31], goals for body weight were not instituted. Improving insulin sensitivity, regardless of weight loss, has been reported to reduce risk of metabolic disease [32]. Further, to avoid stigmatization due to body fatness, focus was placed on improving diet and physical activity rather than on body weight.

#### Consultation with multi-disciplinary and community experts

To inform the multiple components of *TAT*, we collaborated with a team of experts specializing in a wide range of disciplines including nutrition, exercise physiology, public health, psychology, medicine, education, and cultural sensitivity (Table 2). In addition, advice was sought on curriculum, program activities, participant retention strategies, opportunities for program enhancement and expansion, and venues for disseminating research findings.

**Table 2 T2:** Coordinated and Complementary Roles of Research Staff, Consultants and Advisory Board Members for the *Taking Action Together *Project

EXPERTISE	UCB Researchers	Collaborators & Consultants^1^	Board members^2^
**INTERVENTION**			
Adult education	√		√
Cultural relevance		√	√
Curriculum	√		√
Family involvement		√	√
Medical management		√	
Nutrition	√		√
Physical education	√	√	√
Process evaluation	√		
Self-esteem	√	√	√
Study management	√		

**EVALUATION**			
Anthropometry	√	√	√
Biochemical	√	√	√
Diet	√		√
Family demographics & characteristics	√	√	
Physical activity & fitness	√	√	√
Self-esteem & behavior	√	√	√
Statistics & data analysis	√		

**DISSEMINATION**			
Behavioral scientists		√	
Cooperative Extension	√		
Medical community	√	√	√
Research scientists	√	√	√
YMCA and other after-school/community venues			√

^**1 **^Academic collaborators and consultants included researchers at University of California (UC) Berkeley, UC San Francisco, UC Riverside, Brock University in Toronto, and UC Cooperative Extension.

^**2 **^Advisory board members included representation from diverse programs including the Food Stamp and Nutrition Education Program (youth and adult programs), Expanded Food and Nutrition Education Program (EFNEP), 5-a-Day Power Play, Sports Play and Active Recreation for Kids (SPARK), California Adolescent Nutrition and Fitness Program (CanFIT), and the YMCA of the East Bay. Other collaborating institutions and organizations with a long history of involvement in the inner-city Oakland community included Children's Hospital and Research Institute Oakland, the California Department of Health Services and UC county-based Cooperative Extension.

The *TAT *Advisory Board (Table 2) included community members who had successfully developed relevant programs for school-aged children and their families; and members with experience working specifically with inner-city residents and low-income African American families. The Advisory Board was convened yearly; ad hoc consultations with individual members were undertaken as needed. Additionally, we capitalized on established and essential working relationships with local community and state partner organizations including county-based Cooperative Extension programs, and federal USDA-funded food supplementation programs such as FSNEP and EFNEP.

### Control group programming

In contrast to the intervention group, contact with child participants and families in the control group occurred primarily during recruitment and yearly data collection, and there was no hands-on involvement in intervention activities. To encourage participation and maximize study retention while minimizing the 'Hawthorne' effect [33] and dissatisfaction with minimal intervention, control families received information focusing on community opportunities for health promoting activities in the mail monthly, and control children were offered a free week of traditional YMCA summer day camp.

### Trial design, participant recruitment and group assignment

#### Trial design

This controlled, prospective, non-randomized trial was approved by the institutional review board (ethics committees) at the University of California -- Berkeley and San Francisco. Parental informed consent was obtained for all participants. To achieve adequate sample size, three cohorts of participants were recruited over three successive years (Table 3).

**Table 3 T3:** *Taking Action Together *Project Plan - Participants by Group

	Control group	Intervention group
Baseline	Number of participants (boys; girls)	
Cohort 1	51 (21; 30)	52 (20; 32)
Cohort 2	28 (16; 12)	35 (16; 19)
Cohort 3	32 (14; 18)	37 (16; 21)
Total	111 (51; 60)	124 (52; 72)

End of 1^st ^Year Follow-up		
Cohort 1	33 (13; 20)	37 (14; 23)
Cohort 2	20 (11; 9)	18 (7; 11)
Cohort 3	14 (9; 5)	14 (7; 7)
Total	67 (33; 34)	69 (28; 41)

End of 2^nd ^Year Follow-up		
Cohort 1	26 (10; 16)	24 (10; 14)
Cohort 2	12 (6; 6)	11 (7; 4)
Total	38 (16; 22)	35 (17:28)

#### Recruitment

Announcements were distributed at elementary schools and other venues within the targeted communities. Incentives, benefits and risks to participants were conveyed in these announcements. Recruitment was restricted to community venues in regions of Oakland habitated by low income African American families. Because families in these regions tend to be fluid, no restrictions were placed on family structure, ethnicity of the adult caregivers or relationship to the child participant. Data were collected from only 1 child per family. As it happened, similar numbers of families self-selected into each of the two sites and similar numbers were included at baseline (Control group, n = 111; Treatment group, n = 124; Table 3). We expected to achieve a 50:50 ratio for boys:girls, and achieved a ratio at baseline of 44:56.

#### Assessing bias due to motivation

The potential for bias due to motivation was estimated by comparing dropout rates between the two groups during the 1 or 2 year intervention period. Dropout rates for control and intervention groups were similar after both 1 year (40% versus 44%; p = 0.46) and 2 years (66% versus 72%; p = 0.52) of programming. Furthermore, when information collected at baseline was compared for dropouts from the control versus treatment groups, no significant differences were found. As examples, mean baseline insulin resistance (HOMA-IR) values of children who dropped out of the control versus treatment groups during the first year were 2.61 and 2.76, respectively (p = 0.67), and means for dropouts during two years of programming were 2.59 and 2.55, respectively (p = 0.91). Additionally, baseline insulin resistance values for children who completed two years of programming versus those who did not were not significantly different (HOMA-IR mean values: 2.56 and 2.53, respectively; p = 0.90).

#### Reducing bias due to non-randomization

Families self-selected to attend programming at one of the two sites, and this selection preceded information regarding the assignment of treatment to that site; ie. when selecting a site, families did not know whether they would be in the control or the intervention group (Figure 2). Prior to beginning Wave 1, and after families selected their preferred site, a toss of the coin was used to determine which of the two sites would be the intervention site. For subsequent waves, families still were unaware of treatment status when choosing their preferred site. The two sites were similar in many respects including their staffing, characteristics of the facility, economic and cultural characteristics of neighborhood residents, crime rates, and general lack of health care, supermarkets and parks. Although contamination across sites may not have been entirely eliminated, staff (research and YMCA) were alerted to report any interactions that could suggest contamination. We were not made aware of any such reports during the 3-year intervention period.

**Figure 2 F2:**
[figure not shown]
**Flowchart of study participant recruitment, self-selection to site, and eligibility assessment**.

At the analytical stage, statistical analyses for differences by treatment group will be controlled, if needed, for covariates including child age, gender, socioeconomic status, pubertal stage or other potential anthropometric, dietary, physical activity, self esteem, behavior or family confounders (for a comprehensive list of variable assessed, refer to Table 1). The necessity for adjustment for a particular variable will be determined in a preliminary analysis in the following way. Any variable modestly related (p < 0.25) to BOTH treatment group status and the change in the outcome variable will be considered to be a potential confounder and included in analytic models. Since subjects were not randomized into groups, analyses will be statistically adjusted for baseline outcome values (analysis of covariance) as groups may not have been equivalent at baseline for these outcomes (some examples are shown in Table 4).

**Table 4 T4:** Some baseline characteristics of participants in the control and intervention groups (p-value for difference by group).

	Characteristic	Control (mean)	Intervention (mean)	p-value
Child	Age (yr)	9.84	9.85	0.92
	BMI z-score	2.00	2.05	0.52
	Waist-to-hip ratio	0.88	0.89	0.36
	% body fat	36.2	36.3	0.90
	Pubertal stage (1-5 scale)	2.28	2.17	0.54
	Fasting HbA1c (%)	5.18	5.14	0.44
	Fasting HOMA-IR	2.49	2.51	0.94
	Fasting ISI-FFA	0.43	0.42	0.72
	Energy intake (kcal/day)	1829	1887	0.53
	Fat intake (g/day)	75.2	73.0	0.62
	Carbohydrate intake (g/day)	220	245	0.04
	Protein intake (g/day)	71.5	67.9	0.38
	Whole grains intake (servings/day)	0.70	0.73	0.77
	Fruit & vegetable intake (servings/day)	2.06	2.38	0.10
	Dairy intake (servings/day)	1.27	1.21	0.59
	Nutrition knowledge (1-22 scale)	9.63	9.96	0.25
	Food preferences (7-25 scale)	16.0	16.3	0.32
	Snack habits (1-5 scale)	2.41	2.45	0.76
	Fitness (ml O2/min/kg body wt)	41.8	43.8	0.26
	Moderate- & high-intensity physical activity (min/day)	89.7	104.4	0.31
	Global self-worth (1-4 scale)	2.98	3.04	0.55
	Athletic competence (1-4 scale)	2.76	2.82	0.47
Family or Adult	Age of adult responder (yr)	37.1	38.5	0.30
	SEI (4-12 range)	8.42	8.29	0.59
	Family History of T2DM (0-2 scale)	0.13	0.20	0.18
	Intrauterine risk for T2DM (0-2 scale)	0.34	0.32	0.82
	Food habits (7-36 scale)	21.9	23.0	0.04
	Physical activity habits (3-15 scale)	11.7	12.2	0.28
	Family Cohesion (1-4 scale)	3.47	3.45	0.81
	Family Conflict (1-4 scale)	0.94	0.85	0.38

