#### Quantitative data

Quantitative data were managed using computer programs including Microsoft Excel, EpiData, BASC-2 software [34], USDA Nutrient Database [35] and MyPyramid Equivalents Database [36]. Data were double entered and edit checks were incorporated into the data entry program to identify data entry errors. For psychosocial, knowledge and attitude measures, scales will be developed as necessary and compared as described above.

Mean changes in the quantitative outcome variables of interest (HOMA-IR and secondary anthropometric, dietary and activity variables) over one or two intervention years will be evaluated using multiple regression techniques. Adjustment for multiple comparisons will not be made, and with values for p < 0.05 considered statistically significant [37]. In addition, because some of these outcome measures are considered to be intermediary or confounding variables, we will use multiple linear regression to examine the effect of intervention on the primary outcome variable of interest (HOMA-IR), adjusting for baseline HOMA-IR, BMI z-score, psychosocial measures such as self esteem, diet and physical activity behaviors, and other potentially relevant factors such as family and (to account for genetic differences in response to intervention) intrauterine history of T2DM. The correlations of all potential covariates with both the dependent and independent variables will be examined, and variables that correlate at p < 0.25 with both variables will be included in the models.

Initially, we will examine the regression coefficient for intervention status (a dummy variable where 1 = intervention group, 0 = control group) in a simple regression model. Using change in HOMA-IR as one dependent variable example, we will model as follows:

Next, we will examine the effects of other explanatory and/or confounding variables to determine whether they explain the effects of intervention status (if any) using as an example:

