### Outcome and process evaluation

Data collection (Table 1) was designed to allow the effects of intervention to be determined on the primary outcome variable (insulin resistance) and on intermediate outcomes (dietary intakes, physical activity). Changes in behaviors (self efficacy, self esteem) expected to precede changes in primary and intermediate outcomes also were assessed. Finally, collection of data for potential modifiers facilitated increased statistical power by their inclusion, if indicated, as covariates. Outcome evaluations were performed at baseline, and after one and two years of intervention. To maximize objectivity, evaluation staff were different from intervention staff. Process evaluation data were collected to assess the quantity and quality of program services delivered, and responses of child participants, adult participants, paid staff and volunteers (Table 7).

**Table 7 T7:** Process Evaluation Data Collection in *Taking Action Together*

Variables	Methods and Frequency^1^
Adherence to schedule of lessons	Observation - monthly for child component; twice per year for adult component Log - recorded weekly; reviewed monthly
Fidelity of lesson delivery	Observation - monthly for child component; twice yearly for adult component Session evaluation forms - recorded weekly, reviewed monthly
Training, support and monitoring of staff	Observation of attendance and engagement Observation of lesson delivery - bimonthly (child component), twice per year (adult)
Response of participants to sessions	Attendance log - by session; reviewed monthly Session evaluation form - administered lesson-by-lesson (child component), twice per year (adult)
Response of staff and volunteers to sessions	Session evaluation form - administered lesson-by-lesson for child sessions Meeting of staff and volunteers - twice per year
Family response to mailings	Telephone survey - contact intervention families once per year
Overall assessment of program	Confidential telephone survey of intervention families - end of year

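### Admitting a covariate only if it is related at p < 0.25 to both arm and outcome change discards balanced prognostic covariates, at a modest cost in precision; a short fixed set would be better

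*Protocol article*

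**What the plan says.** Under Reducing bias due to non-randomization, the protocol article says that group comparisons "will be controlled, if needed, for covariates including child age, gender, socioeconomic status, pubertal stage" and other potential confounders. It then defines need by a preliminary test: "Any variable modestly related (p < 0.25) to BOTH treatment group status and the change in the outcome variable" counts as a potential confounder and goes into the model. The baseline value of the outcome is adjusted for in any case and does not have to pass the test.

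The Quantitative data section repeats the rule: "variables that correlate at p < 0.25 with both variables will be included in the models". Just before that, it describes a HOMA-IR model adjusted for baseline HOMA-IR, BMI z-score, psychosocial and behavioural measures, and family and intrauterine history of T2DM. It does not say whether those named terms must also pass the screen.

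Two other statements bear on the point. The Theoretical model section says that "several factors (e.g., child pubertal stage, self esteem, psycho-behavioral status) are able to interfere with or promote these relationships". The Outcome and process evaluation section says that data on potential modifiers "facilitated increased statistical power by their inclusion, if indicated, as covariates".

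**The concern.** A covariate can help in two ways. If it differs between arms and predicts the outcome, adjustment removes bias. If it predicts the outcome but is balanced, adjustment removes residual variance and sharpens the treatment estimate. The rule recognises only the first. By requiring a relation to arm, it bars the covariates that would add precision at least cost.

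The arm half of the test is also a weak guide to confounding here. Families chose between two sites, and a p-value above 0.25 at this sample size does not show that confounding is absent. The other half selects covariates on the same outcome data that are then used to test the intervention, so the final model depends on the data and its standard error takes no account of the selection.

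At stake are the precision and calibration of the primary comparison, in a study that fell from 111 and 124 children at baseline to 67 and 69 at year 1 and 38 and 35 at year 2 (Table 3).

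**Working it through.** **The plan's own figures.** The plan gives no figure for the covariate rule. Its sample size does not depend on the rule: 2 × (1.96 + 0.84)² × 7.2² / 4² ≈ 51 per group, against the stated 50, with no covariate term. The planned difference is 4 / 7.2 = 0.56 SD of insulin, so the 0.5 SD used below is of the same order.

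**Step 1: which named covariates pass the arm test at baseline?** Table 4 prints p-values for three of them. Sex has none, so it is computed from Table 3.

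- Age: 0.92. Socioeconomic index: 0.59. Pubertal stage: 0.54.
- Sex at baseline: boys 51/111 = 45.9% v 52/124 = 41.9%. Pooled proportion 103/235 = 0.438; SE = √[0.438 × 0.562 × (1/111 + 1/124)] = 0.065; z = 0.040/0.065 = 0.62; p = 0.54.
- Sex in year-1 completers: 33/67 = 49.3% v 28/69 = 40.6%; SE = 0.085; z = 1.02; p = 0.31.

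All exceed 0.25, so on these figures none of the four could enter, whatever its relation to HOMA-IR change.

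**Step 2: how unbalanced are they?** The implied standardised difference is t × √(1/n₁ + 1/n₂), where t is the value that gives the printed p. At 111/124 the root is 0.131.

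- Age: 0.101 × 0.131 = 0.01.
- Pubertal stage: 0.614 × 0.131 = 0.08.
- Socioeconomic index: 0.540 × 0.131 = 0.07.

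The largest difference that still fails the screen (p = 0.25) is about 0.15 SD at 111/124, 0.20 SD at 67/69 and 0.27 SD at 38/35. The screen becomes more permissive of imbalance as follow-up shrinks.

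**Step 3: what does the rule cost?** This was simulated with 67 and 69 children and four independent normal covariates, each with correlation r with the outcome. The baseline outcome was not in the model, so r should be read as correlation remaining after baseline adjustment, and the 0.5 SD effect as a fraction of the SD that remains. Both are assumptions. Monte Carlo error is about one percentage point.

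| r for each covariate | Variance explained, 4r² | Power for 0.5 SD: rule | Power: all four fixed | Test size under rule (nominal 5%) | Bias under rule, true 0.1 SD imbalance in all four |
|---|---|---|---|---|---|
| 0.1 | 4% | 83% | 84% | about 5% | about 0.01 SD |
| 0.2 | 16% | 84% | 88% | about 4% | about 0.02 SD |
| 0.3 | 36% | 88% | 95% | about 3% | about 0.03 SD |

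With all four fixed, bias is about zero and test size about 5%. With no adjustment, bias would be 4 × 0.1 × r = 0.04, 0.08 and 0.12 SD, so the rule removes most of it.

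The test is conservative for a simple reason. The rule adjusts mainly when a prognostic covariate happens to be unbalanced, which narrows the true spread of the estimate. When covariates stay out, their variance remains in the residual, so the reported standard error is too large for that spread.

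**The case against.** The strongest reply is that the effect is small and its size rests on assumptions. No covariate-outcome correlation is published. At r = 0.1 the rule costs about one point of power. The largest loss needs four independent covariates that together explain 36% of the remaining variance, which is a lot to ask when age is confined to 9–10 years and age, sex and pubertal stage are unlikely to be independent. The baseline outcome is adjusted for regardless, which already recovers precision. Even the rule's power in these scenarios exceeds the 80% planned. All of this stands, and it limits the size of the point.

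Four stronger readings may tempt a reader, and the documents do not support them.

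- **That the four variables are certain to be shut out.** Exclusion is shown only for the baseline sample. The screen also needs outcome change, so it would presumably run on children with follow-up. There, only sex can be checked.
- **That confounding control is lost.** Age, pubertal stage and socioeconomic index fail the arm test because they are nearly balanced. A bias of 0.03 SD is about a fifth of the simulated standard error (0.15), and it requires all four imbalances to push the same way.
- **That false positives are inflated.** Test size stays at or below about 5%.
- **That the plan contradicts its own claim of added power.** The claim is for inclusion "if indicated" in effect: it is conditional, which is compatible with a screen. Likewise, the HOMA-IR model in the Quantitative data section names BMI z-score (arm p = 0.52) and intrauterine history (0.82), but the text leaves open whether they are screened, so their exclusion is not established.

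None of these replies gives a reason to prefer the rule to a fixed set.

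**Conclusion.** The point holds as a modest one about precision. The rule is stated twice and discards covariates that are prognostic but balanced; on the published baseline figures it would drop age, sex, pubertal stage and socioeconomic index. The cost ranges from about 1 to 7 percentage points of power for a 0.5 SD effect at year 1, as the assumed correlation of each covariate rises from 0.1 to 0.3, with a test that is slightly conservative. Residual measured confounding is about 0.01–0.03 SD under the assumed common 0.1 SD imbalance. That is small, although in a self-selected two-site comparison a non-significant arm difference should not be read as evidence that confounding is absent. Year 2 was not simulated; with 38 and 35 children, imbalances of up to about 0.27 SD could go unadjusted.

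**What to change.** In the primary HOMA-IR model, replace the two-way p-value screen with a short baseline set that is already collected: baseline outcome, age, sex, pubertal stage, BMI z-score and socioeconomic index, all entered whatever their p-values. Do not select covariates on the outcome data. Report any screened or further-adjusted model only as a sensitivity analysis, and say whether the terms named for the further HOMA-IR model in the Quantitative data section are fixed or screened.

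The change is to wording only and needs no new data. With pubertal stage entered as a single score, it costs five degrees of freedom beyond the baseline outcome already planned. Counting intercept, arm and baseline outcome, eight parameters leave 136 − 8 = 128 residual degrees of freedom at year 1 and 73 − 8 = 65 at year 2, where the cost is somewhat larger but still acceptable.
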